### Randomization and blinding

The generated random tables were developed with Statistical Analysis System (SAS, version 9.4) by randomization biostatisticians. All the participants were included in the clinical trial according to the order of random table numbers. The ratio of the two groups was 1:1. For blinding, 260 sealed opaque envelopes were used to keep the allocation code for each participant, which were not accessible to the researchers, participants, clinical trial pharmacists, data managers, or statisticians. The BSJY granule was similar to its placebo in each group. The manufacturer, Sichuan Neo-Green Pharmaceutical Technology Development Co., Ltd., labeled the random codes on the package according to the principles of GCP.

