### Statistical analysis

#### Sample size calculation

The formula used to calculate the sample size is as follows, which is based on superiority clinical trial interval hypothesis test sample size estimation [52]. The sample size was calculated based on the expected reduction in reducing of BP. One previous study suggested that the reduction of BP after interventional treatment is 4.5 mmHg, and the BP SD is 10 mmHg. Therefore, we assume the reduction of BP as 4.5 mmHg in this study. In the following formula, *c* is the ratio between two sample cases, *n*1 = *n*2, so *c* = 1. *σ* is the BP SD 10 mmHg, and *δ* is the expected effect BP 4.5 mmHg, so *σ* = 10 and *δ* = 4.5. Given a type I error rate of *α* = 0.05, a power of 90% (type II error rate of *β* = 0.1), so *uα* = 1.96, *uβ* = 1.282. *n1* = *n2* ≈ 104, the sample size for one group needs to be 104, resulting in *n* = 2 × 104 = 208 patients. Considering the maximum possible dropout rate is 20%, a total of 260 patients needs to be allocated to reach the required number of patients for the efficacy analysis.
$$ {\displaystyle \begin{array}{c}{n}_1={\left[\frac{\left( u\alpha + u\beta \right)\sigma }{\delta}\right]}^2\frac{\left(1+c\right)}{c},{n}_2=c{n}_1\\ {}{n}_1={n}_2\approx 104\end{array}} $$

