#### Planned data analysis

The intention-to-treat principle will be used to analyze the efficacy and safety of BSJY. The independent data administrator and the professional statistician will undertake data entry and data management, and perform the data analysis, respectively. All the efficacy and safety analyses with all randomly assigned participants included will be conducted within the full analysis set (FAS). The per-protocol set (PPS) analysis will also be conducted to compare the results from FAS and PPS. Demographic and laboratory characteristics will be calculated at baseline and after the treatment period for all patients. The statistical analysis will be done at Guang’anmen Hospital, China Academy of Chinese Medical Sciences in Beijing.

For continuous variables with normal distribution, the comparability of the characteristics between the two study groups will be assessed by using the *t*-test. While for the comparison of data with non-normal distribution, the non-parametric Mann-Whitney-Wilcoxon test will be used. Continuous variables will be expressed by mean ± SD. We will assess the paired *t*-test to compare the difference of the outcome between preintervention and postintervention in each group by using the independent *t*-test. A *χ*^2^ test will be used for categorical variables, while the Fisher exact test will be used when the theoretical frequency is less than 5 in more than 25% of the cells. Categorical variables will be shown as counts and percentages. Whether the hypothesis of superiority is available will be judged by comparing the 95%CI of the difference in intergroup efficacy. All statistical tests are unilateral tests; *p* < 0.05 is statistically significant. All statistical analyses will be performed using SPSS V.20.0.

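### The trial is sized with a critical value of 1.96, but the analysis section makes every test one-sided at p < 0.05, so the analysis rule does not match the design

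*Protocol article*

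**What the plan says.** Three statements in the protocol article bear on the error rate.

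- **Sample size calculation.** Alpha is given as 0.05 without a sidedness, and the critical values follow: "so *uα* = 1.96, *uβ* = 1.282". Power is stated as "a power of 90% (type II error rate of *β* = 0.1"), and the effect and SD as "so *σ* = 10 and *δ* = 4.5" (mmHg). The result is 104 per group and 208 in all. Then: "Considering the maximum possible dropout rate is 20%, a total of 260 patients needs to be allocated".
- **Planned data analysis, superiority.** "Whether the hypothesis of superiority is available will be judged by comparing the 95%CI of the difference in intergroup efficacy". The section does not say whether the interval is one-sided or two-sided.
- **Planned data analysis, next sentence.** "All statistical tests are unilateral tests", with p < 0.05 as the significance level. No direction is named for any test, and no class of comparison is exempted. The same section covers efficacy, safety and baseline comparability, using t-tests, Mann-Whitney-Wilcoxon, chi-square and Fisher tests.

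**The concern.** A critical value of 1.96 leaves 2.5% in the direction of benefit. A one-sided test at 0.05 leaves 5%. These are different standards of evidence for the same hypothesis, and the article does not reconcile them.

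The conclusion on efficacy is at stake. A result with a one-sided p between 0.025 and 0.05 meets the p-value rule but falls short of the standard for which the trial was sized. If both rules stay in the plan, someone must choose between them, possibly with the result in view.

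The word 'all' adds a second difficulty. Baseline imbalance has no favoured direction, a safety comparison needs its direction stated before a one-sided test means anything, and a chi-square test on more than two rows or columns has no one-sided form.

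**Working it through.** **Inputs.** Effect 4.5 mmHg, SD 10 mmHg, power 90% (1.282), critical value 1.96 and dropout 20%, all from Sample size calculation; 1:1 allocation from Randomization and blinding. The value 1.645 is the normal quantile for one-sided 0.05.

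**1. Reproduce the plan's figure.** With equal arms the article's formula is n = 2 × [(uα + uβ) × σ / δ]².

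- With 1.96: 2 × [(1.96 + 1.282) × 10 / 4.5]² = 2 × 7.204² = 103.8, so 104 per arm, 208 evaluable, and 208 / 0.8 = 260. All three stated figures are reproduced.
- With 1.645: 2 × [(1.645 + 1.282) × 10 / 4.5]² = 84.6, so 85 per arm, 170 evaluable, and 170 / 0.8 = 212.5, so 213.

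The design therefore rests on two-sided 0.05, or equivalently one-sided 0.025. One-sided 0.05 does not give the trial's size.

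**2. Success thresholds at 104 per arm.** SE = 10 × √(2/104) = 1.387 mmHg.

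- One-sided p < 0.05: 1.645 × 1.387 = 2.28 mmHg.
- Two-sided 95% CI excludes zero: 1.96 × 1.387 = 2.72 mmHg.

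Observed differences between these values pass one rule and fail the other.

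**3. The same at 130 per arm.** The full analysis set is to include all randomised participants. If all 260 contribute data, SE = 10 × √(2/130) = 1.240 mmHg and the thresholds are 2.04 and 2.43 mmHg. The band moves but does not close.

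**4. Error and power at 104 per arm.** Standardised effect: 4.5 / 1.387 = 3.245.

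| Rule | Per-test false claim of benefit | Power at 4.5 mmHg |
|---|---|---|
| Critical value 1.96 | 2.5% | Φ(3.245 − 1.96) = 90.1% |
| Critical value 1.645 | 5.0% | Φ(3.245 − 1.645) = 94.5% |

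**5. How often the band matters.** As an illustration, take a true effect of half the planned one, 2.25 mmHg. Then 2.25 / 1.387 = 1.622, and the chance of landing in the band is Φ(1.96 − 1.622) − Φ(1.645 − 1.622), about 12%.

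**6. The three statements side by side.**

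| Reading of the 95% CI | Agrees with 1.96? | Agrees with one-sided p < 0.05? |
|---|---|---|
| Two-sided | Yes | No |
| One-sided | No | Yes |

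Neither reading makes all three statements consistent.

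**The case against.** The best defence is that the article assigns the superiority decision to the confidence interval, while the p-value sentence is a general rule for tests. If the CI is two-sided and governs, the superiority claim stays at 2.5% in the direction of benefit. If the CI is one-sided, it agrees with the p-value sentence, and the two adjacent sentences do not conflict. This stands, and it limits the point in two ways.

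- A reader might infer that the two neighbouring sentences certainly contradict each other. They do so only if the CI is two-sided. That is the usual meaning of an unqualified 95% CI, but the article does not say it.
- A reader might infer that the trial's false-positive rate doubles. The step from 2.5% to 5% is relative to the standard implied by 1.96, and it occurs only if the one-sided p-value rule or a one-sided CI decides. A single one-sided test at 0.05 does not exceed the stated alpha of 0.05. Both figures are also per test. Several blood pressure measures are listed under the primary outcome, so neither is a trial-wide rate.

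The defence can add three things. The trial is not underpowered under either rule, since 104 per arm exceeds the 85 that one-sided 0.05 would need. The thresholds of 2.28 and 2.72 mmHg assume the maximum dropout. And it would go too far to say that the safety tests cannot flag harm: that assumes they point towards benefit, a direction the article does not give, and adverse events are recorded and reported whatever any test shows. All three are fair.

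None of this removes the mismatch between the 1.96 in the sample size section and the one-sided p < 0.05 in the analysis section, which holds on either reading of the CI. Nor is it a detail left to a later plan: the article states both rules outright.

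**Conclusion.** The point holds as a mismatch between design and analysis. The sample size uses 1.96 and gives 104 per arm; the stated test rule implies 1.645 and would need 85.

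The further consequences are conditional:

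- If the CI is two-sided, it conflicts with the adjacent p-value rule for observed differences of about 2.28 to 2.72 mmHg (SD 10, 104 per arm), or 2.04 to 2.43 mmHg if all 130 per arm contribute.
- If the one-sided p-value rule or a one-sided CI decides, the per-test chance of a false claim of benefit is 5% where the design implied 2.5%, and power at 4.5 mmHg is 94.5% where the design gives 90.1%.

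The sample size arithmetic is correct and the planned total is adequate under either rule. Separately, the one-sided rule as worded gives no direction for safety and baseline comparisons, and it cannot be applied to chi-square tables larger than 2x2. These figures use the normal approximation and the article's own effect and SD.

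**What to change.** Replace the sentence on unilateral tests with:

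> All tests are two-sided at alpha = 0.05. Superiority is concluded when the two-sided 95% CI for the between-group difference excludes 0 in favour of BSJY.

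For efficacy, one-sided testing at 0.025 with the same two-sided 95% CI is equivalent, should the sponsor prefer to keep a directional hypothesis. Safety, baseline and secondary comparisons should be two-sided in either case. The sample size section should state that its alpha of 0.05 is two-sided.

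The sizes of 104, 208 and 260 do not change, and power at 104 per arm is the planned 90%. The only cost is a stricter success threshold than the p-value sentence would allow: 2.72 instead of 2.28 mmHg at 104 per arm. The change should be made and dated before unblinding. The article reports that no analysis had been conducted when the manuscript was submitted; it does not show the present state of the trial.

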## Discussion

Hypertension, as one of the most important risk factors for cardiovascular disease, and its treatment and control rates are still low worldwide [53]. Better treatment methods with fewer side effects are required, which was the motivation to apply BSJY in this research. In this trial, we will assess the efficacy and safety of BSJY in treating patients with low-to-medium risk hypertension.

According to our previous studies, BSJY can promote the expression of the ERK pathway and inhibit the expression of the TNF-α, MCP-1, and IL-6, which would suppress ventricular hypertrophy and inflammatory responses. Furthermore, BSJY may lower BP and protect the target organs of hypertension including the heart and kidney by inhibiting TGF-β1/Smads signaling molecules in spontaneously hypertensive rats [54]. Based on network pharmacology, 93 active ingredients were predicted for BSJY involving 566 core targets, including 50 direct targets, such as epinephrine receptor, adenosine receptor, endothelin receptor, nitric oxide synthase, and glucose kinases, involved in the regulation of calcium and sodium ion transport, vascular endothelial function, glucose and lipid metabolism, and other related biological processes and signaling pathways [55]. Liquid chromatography-mass spectrometry analysis of BSJY also has been conducted to evaluate its chemical components. It mainly contains tartaric acid, gallic acid, gastrodin, catalpol, neochlorogenic acid, 2-[4-(b-d-glucopyranosyloxy) benzyl] citrate, morroniside, chlorogenic acid, oxypaeoniflorin, cryptochlorogenic acid, loganin, parishin B, pinoresinol di-*O*-Glc, parishin C, quercetin-3-*O*-sambubioside, suffruticoside A or B or C or D, galloylpaeoniflorin, and iso-Mudanpioside H. However, there is a lack of high-quality clinical research on the supposed benefits of BSJY.

Pharmacogenomic evaluation of antihypertensive responses offers the clinical promise of individualization of therapy based on a person’s genetic makeup [11]. It is said that the loci/SNPs associated with BP/hypertension are also associated with BP response to antihypertensive drugs [10]. This is the first paper that researches pharmacogenomic evaluation of antihypertensive responses in TCM. The present study is designed as a double-blind, randomized, placebo-controlled trial that will provide high-powered evidence regarding the efficacy, safety, and pharmacogenomic evaluation of BSJY in treating patients with low-to-medium risk hypertension. The progress and quality of the trial will be monitored by a clinical research organization of Guang’anmen Hospital.

There are also some limitations to this study. First, we supposed to test twenty single nucleotide polymorphisms (SNPs) that have been associated with BP in genome-wide association studies in Asian people. It is different that significant genetic loci for BP and hypertension reported in genome-wide association studies in Europeans, Asians, and Africans. It should be considered that the complexity of the genetic mechanisms underlying hypertension and the need for much larger sample sizes when looking for genes associated with BP. For TCM, it can be viewed as a very important environment element to pharmacogenomic evaluation. Second, our multi-center experiments will be conducted in China in the future.

### Trial status

Patient recruitment began in November 2019 and was expected to be completed in December 2022. At the time of manuscript submission, 80 patients had been recruited and completed the 9-week follow-up. Currently, we are still recruiting participants. However, no analysis has been conducted since the commencement of the trial. No serious AEs have occurred to date.
